# Traditional invasive vs. minimally invasive esophagectomy: a multi-center, randomized trial (TIME-trial)

**DOI:** 10.1186/1471-2482-11-2

**Published:** 2011-01-12

## Abstract

**Background:**

There is a rise in incidence of esophageal carcinoma due to increasing incidence of adenocarcinoma. Probably the only curative option to date is the use of neoadjuvant therapy followed by surgical resection. Traditional open esophageal resection is associated with a high morbidity and mortality rate. Furthermore, this approach involves long intensive care unit stay, in-hospital stay and long recovery period. Minimally invasive esophagectomy could reduce the morbidity and accelerate the post-operative recovery.

**Methods/Design:**

Comparison between traditional open and minimally invasive esophagectomy in a multi-center, randomized trial. Patients with a resectable intrathoracic esophageal carcinoma, including the gastro-esophageal junction tumors (Siewert I) are eligible for inclusion. Prior thoracic surgery and cervical esophageal carcinoma are indications for exclusion. The surgical technique involves a right thoracotomy with lung blockade and laparotomy either with a cervical or thoracic anastomosis for the traditional group. The minimally invasive procedure involves a right thoracoscopy in prone position with a single lumen tube and laparoscopy either with a cervical or thoracic anastomosis. All patients in both groups will undergo identical pre-operative and post-operative protocol. Primary endpoint of this study are post-operative respiratory complications within the first two post-operative weeks confirmed by clinical, radiological and sputum culture data. Secondary endpoints are the operative data, the post-operative data and oncological data such as quality of the specimen and survival. Operative data include duration of the operation, blood loss and conversion to open procedure. Post-operative data include morbidity (major and minor), quality of life tests and hospital stay.

Based on current literature and the experience of all participating centers, an incidence of pulmonary complications for 57% in the traditional arm and 29% in the minimally invasive arm, it is estimated that per arm 48 patients are needed. This is based on a two-sided significance level (alpha) of 0.05 and a power of 0.80. Knowing that approximately 20% of the patients will be excluded, we will randomize 60 patients per arm.

**Discussion:**

The TIME-trial is a prospective, multi-center, randomized study to define the role of minimally invasive esophageal resection in patients with resectable intrathoracic and junction esophageal cancer.

**Trial registration (Netherlands Trial Register):**

NTR2452

## Background

The incidence of esophageal cancer is increasing in the Western world. In the Netherlands, in the year 1990 some 807 patients were diagnosed with esophageal cancer, whereas in 2005, this number reached a staggering 1546 [1]. It is expected that this rise in incidence will continue in the years to come. This substantial increase in incidence can be accounted for by an increase in the number of adenocarcinomas diagnosed.

Approximately one third of the patients are considered candidates for a curative approach. Surgical resection with radical lymphadenectomy, usually after neoadjuvant chemotherapy or chemo-radiotherapy, remains the only curative option for resectable esophageal cancer. Surgery is considered when the tumor is staged as cT1-3 N0-1 M0. Despite the curative intent, some 30% of all resections have microscopically residual disease (R_1_). Most patients present with stage III esophageal cancer, which has a 5-year survival of approximately 20-25% [2]. In addition, the possible value of neoadjuvant chemoradiotherapy or chemotherapy is currently being investigated. However, a meta-analysis by Gebski et al. has shown that surgery following chemoradiotherapy for both squamous cell carcinoma and adenocarcinoma has a survival benefit of 13% after 2 years. For neoadjuvant chemotherapy this survival benefit was 7% after 2 years for adenocarcinomas [3].

The three main surgical approaches utilized worldwide for intrathoracic esophageal cancer are the following: (1) the three stage transthoracic resection (i.e. right postero-lateral thoracotomy, laparotomy and cervicotomy) with a cervical anastomosis; (2) the two stage transthoracic resection (i.e. laparotomy, and right postero-lateral thoracotomy, including the Ivor Lewis approach with an intrathoracic anastomosis); and (3) the two stage transhiatal resection (i.e. laparotomy and cervicotomy with cervical anastomosis) [4]. Transhiatal esophagectomy according to Orringer is generally performed for gastro-esophageal junction cancers [5]. Nevertheless, cancer of the lower esophagus metastasized, according to the Tumor-Node-Metastasis classification, in more than 45% to the lymph nodes in mediastinum and carina. Therefore patients with reasonable general condition are increasingly surgically approached transthoracically. In the randomized study by Hulscher et al. and long term follow-up, comparing the transhiatal and transthoracic esophageal resection, an important trend of better survival has been observed in the transthoracically approached patients [6,7]. This transthoracic procedure is associated with a high morbidity and mortality rate of approximately 50-70% and 5% respectively [6]. Moreover, the extensive nature of this open approach has a significant negative impact on the quality of life of these patients and is associated with a long in-hospital recovery.

Minimally invasive esophageal (MIE) resection for cancer avoiding the thoracotomy and laparotomy can reduce the amount of trauma of the required surgery with the same oncological value. This will imply a reduction of the post-operative morbidity, a shortening of the recovery time and an increase of quality of life. Evidence of the short term benefits of minimally invasive surgery over open procedures with similar oncological outcome is accumulating. Less perioperative complications, shorter hospital stay and faster post-operative recovery appear to be the main advantages. MIE involves a right thoracoscopy and laparoscopy, either with a cervical or intrathoracic anastomosis. The thoracic phase of this procedure can be performed through a lateral right thoracic approach with a right lung block by selective intubation or in prone position without selective lung block. This prone approach, with partial lung collapse, will result in lower percentage of pulmonary complications [8,9].

To date, no randomized trials have been performed comparing any modality of minimally invasive esophagectomy with an open traditional approach [10]. Given the values of postoperative morbidity, quality of life and quality of the specimen, the aim of this prospective randomized study is to compare the MIE by right thoracoscopy in prone position and laparoscopy with the open esophageal resection by right thoracotomy and laparotomy in left lateral decubitus, for those patients possessing intrathoracic resectable esophageal cancer. This comparison will provide further evidence supporting the minimally invasive and cost-effective approach for esophageal cancer.

## Methods

### Study objectives

The TIME trial is prospective, multi-center, randomized study comparing traditional transthoracic esophageal resection with minimally invasive resection for esophageal cancer. Patients with resectable intrathoracic esophageal cancer are randomized for either (a) minimally invasive transthoracic esophageal resection in prone position or (b) traditional open transthoracic esophageal resection. Our hypothesis is that patients undergoing a minimally invasive esophagectomy have fewer morbidity, a shorter duration of the intensive care unit (ICU) admission and a better quality of life than following the traditional approach.

### Endpoints

The primary endpoint of this study concerns the respiratory complications (i.e. infections) within two weeks after the operation. This is categorized as: grade 1) initial respiratory distress after operation with continuation of mechanical ventilation; grade 2) after successful detubation, clinical manifestation of respiratory infection caused by (broncho) pneumonia, confirmed by thorax X-ray or CT scan of the thorax and a positive sputum culture; and grade 3) other thoracic infections like post-operative empyema either caused or not by leakage from the gastric conduit necessitating drainage or reoperation [modified from Hulzebos et al., [11]]. Consequences for patients range from extensive physiotherapy, involving oxygen and specific antibiotics to intubation and mechanical ventilation. Furthermore, important respiratory deterioration after extubation, involving reintubation and mechanical ventilation will lead to the necessity of a CT scan of the thorax and abdomen, and thus endoscopic examination of the gastric tube and anastomosis in order to rule out a leakage.

The secondary endpoints are operation related events (e.g. duration of operation, blood-loss and conversion to open procedure in MIE group) and re-operations. Moreover, general morbidity (major and minor) is recorded. Minor complications are defined as wound infections, venous thrombosis or other. Major complications consist of- apart from respiratory complications- post-operative bleeding, anastomosis leakage, mediastinitis, and re-operations within the in-hospital period. Furthermore, post-operative recovery data are length of ICU and hospital stay (days), type and number of analgesics needed after operation, VAS-pain-score, return to fluid and normal diet, quality of life questionnaires (SF-36 and EORTC QLQ-OES18) [12], and quality of the specimen resected (length of specimen, number and location of lymph nodes resected, and circumferential resection margin). Also hospital mortality and readmissions are recorded. Furthermore survival will be analyzed.

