### Power of the study

According to the published literature and own experience at the VU university medical center a difference in respiratory infections of 28% is found between the traditional open procedure (57%) and the MIE procedure (29%) [6,7,9,13-15]. To demonstrate this difference of 28%, using a alpha = 0.05 and beta = 0.80, two groups of 48 patients are needed. This is based on a two-sided significance level (alpha) of 0.05 and a power of 0.80. Estimating that approximately 20% of the patients may be excluded, 60 patients will be randomized per arm.

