### Post-operative management

Patients in both groups will receive similar post-operative treatment. All patients will after surgery be admitted intubated at the intensive care unit (ICU). After stabilization and detubation, the patient will if indicated be admitted to the general surgical ward or to the medium care unit (MCU). In the first days after surgery analgesics are administered by the epidural route. In the event of epidural failure, post-operative pain will be treated intravenously by a 'patient controlled analgesia' (PCA); when necessary through a pump with morphine. Patients will be instructed about the PCA pump by an anesthesiologist and morphine doses will be noted. Patients will have a nasogastric tube in-situ for at least 5 days as some gastric conduit distension is expected. All patients will receive postoperative physiotherapy for breathing-exercises the day after surgery. To regain early mobilization, starting day 1, patients are encouraged to sit out of bed in the general surgical ward. Enteral feeding is commenced day 1 after operation through the jejunostomy and increased to optimal feeding at day 3. At day 5, after gastrographine swallow X ray, the nasogastric tube is retired and started with liquids. Normal diet can be progressively resumed while jejunostomy feeding is decreased. Patients will be discharged when they are able to eat normal food, can walk and are comfortable with oral analgesia. Delay to "social" reasons will be noted. Completion of the feeding over the jejunostomy may be continued after discharge. Patient follow-ups are carried out at the outpatient clinic at 6 weeks, 3 months, 6 months and 1 year after discharge. During these visits, the quality of life questionnaires (SF-36 and EORTC QLQ-OES18) will be completed. The regular follow-up will continue up to 5 years after surgery.

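### The primary endpoint is called confirmed infection, but its first grade needs neither infection nor confirmation, so the same patient can be an event or a non-event

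*Protocol article*

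**What the plan says.** Four places in the protocol article describe the primary outcome or the rates that it was planned on.

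- **Abstract, Methods/Design:** the endpoint is "post-operative respiratory complications within the first two post-operative weeks confirmed by clinical, radiological and sputum culture data". The rates of 57% and 29% are called pulmonary complications.
- **Endpoints:** "The primary endpoint of this study concerns the respiratory complications (i.e. infections) within two weeks after the operation". Three grades follow. Grade 1 is "grade 1) initial respiratory distress after operation with continuation of mechanical ventilation". Grade 2 is respiratory infection from (broncho)pneumonia after successful detubation, "confirmed by thorax X-ray or CT scan of the thorax and a positive sputum culture". Grade 3 is other thoracic infection, such as empyema with or without leakage, that needs drainage or reoperation.
- **Power of the study:** "a difference in respiratory infections of 28% is found", namely 57% open against 29% minimally invasive (MIE). This leads to 48 per arm, and 60 per arm randomized.
- **Discussion:** the 57% comes from an earlier open series, where it is described as pulmonary complications.

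Post-operative management adds that every patient reaches the ICU still intubated and is detubated after stabilization.

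**The concern.** A primary outcome has to sort each patient into event or non-event in one way only. Here the label (infection), the confirmation requirement (clinical, imaging and culture) and the grade list give different answers for the same patient. Grade 1 is the clearest case, but grades 2 and 3 have gaps as well.

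Two things are at stake. First, with no statement of which grades count, the definition could be settled once results are known. Second, the planning rates carry two labels, so it is unclear which outcome has the stated 80% power.

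**Working it through.** **1. Classifying patients under each wording**

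| Patient, within two weeks | Grade list | Equated with infections (Endpoints) | Abstract confirmation wording |
|---|---|---|---|
| Distress, ventilation continued, no infection | Event (grade 1) | Not an event | Not an event |
| Pneumonia after detubation, imaging and culture positive | Event (grade 2) | Event | Event |
| Pneumonia, never extubated | Not grade 2; an event only if another grade is met | Event | Event if confirmed |
| Empyema drained, no positive sputum culture | Event (grade 3) | Event | Not an event |

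Only the second row gets the same answer throughout.

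**2. The plan's sample size**

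Inputs from Power of the study: p1 = 0.57, p2 = 0.29, two-sided alpha 0.05, power 0.80. The mean rate is 0.43.

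n = [1.960·√(2·0.43·0.57) + 0.842·√(0.57·0.43 + 0.29·0.71)]² / 0.28² = (1.372 + 0.565)² / 0.0784 = 47.9, so 48 per arm. Then 48 / 0.80 = 60. Both stated figures reproduce.

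**3. If 57% and 29% are infection-only rates**

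Assume that grade 1 alone strikes a fraction g of the non-infected patients, equally in both arms. The all-grade rate is p + (1 − p)·g. For g = 0.10 this gives 0.57 + 0.43·0.10 = 0.613 and 0.29 + 0.71·0.10 = 0.361. Power is by exact binomial enumeration of the uncorrected chi-square test.

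| g (assumed) | Open | MIE | Power, 48 per arm | Power, 60 per arm, no exclusions |
|---|---|---|---|---|
| 0 | 57.0% | 29.0% | 80% | 89% |
| 5% | 59.2% | 32.6% | 76% | 85% |
| 10% | 61.3% | 36.1% | 71% | 81% |
| 20% | 65.6% | 43.2% | 61% | 71% |
| 30% | 69.9% | 50.3% | 50% | 60% |

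**4. If 57% and 29% already include grade 1**

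An infection-only endpoint then has lower rates. The points removed are assumed, and power is by the normal approximation, which agrees with exact enumeration to within 1 percentage point.

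| Points removed, open/MIE | Open | MIE | Power, 48 per arm |
|---|---|---|---|
| 5/5 | 52% | 24% | 82% |
| 10/5 | 47% | 24% | 66% |
| 15/5 | 42% | 24% | 47% |

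**5. Could grade 1 alone produce a positive result?**

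Assume infection at 30% in both arms and grade 1 at 5% in the MIE arm. With grade 1 at 10% in the open arm, the all-grade rates are 37% and 33.5%, and the test favours MIE in about 5% of trials at 48 per arm, against a nominal 2.5%. With 30% in the open arm (51% and 33.5%) the figure is 41%. That last figure needs a 25-point gap in grade 1, for which the documents give no support.

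**The case against.** The best defence is that the Abstract and the parenthesis in Endpoints are shorthand, and that the grade list is the operative definition. An article condenses, and thresholds such as a minimum ventilation time may well sit in the full protocol. That is fair for thresholds, and their absence is not part of this point. It does not remove the conflict: the sentence that introduces the grades itself equates the endpoint with infections, and the power section repeats that label. These are printed statements that disagree.

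Some stronger readings are tempting but not supported:

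- **Extubation practice could decide the trial.** A reader might infer this because all patients arrive intubated and the arms differ in lung block. But grade 1 requires respiratory distress as well as continued ventilation, so routine ventilation is not an event. Both groups are to receive similar post-operative care, and randomization is stratified by center. Avoiding lung block is largely part of the minimally invasive procedure, so a real difference in early distress may be a treatment effect. The documents do not discuss blinding and give no grade 1 rate. This remains a possibility only.
- **Reintubation for deterioration counts only if culture-positive.** Grade 3 states no culture requirement, and the CT and endoscopy that follow reintubation can lead to grade 2 or grade 3.
- **Grade 1 necessarily dilutes power.** This assumes that the planning rates are infection-only. The Abstract and Discussion call them pulmonary complications, and if they include grade 1, adding it again double-counts. Even under the dilution assumption, the 10% case keeps about 81% power if all 60 per arm are analysed.
- **Grades 2 and 3 alone are the only sound endpoint.** Step 4 shows that this choice can itself lose power.

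**Conclusion.** The point holds as an inconsistency in the primary outcome. It rests on the printed text and needs no assumption: infection, universal confirmation and the three grades cannot all be true of one endpoint, and no passage says which grades form the comparison. The sample-size arithmetic is correct; what is unclear is the outcome that it belongs to.

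The numerical effect depends wholly on assumed grade 1 rates. At 48 per arm, power runs from 76% down to 50% if equal grade 1 rates of 5-30% are added to infection-only planning rates. It runs from 82% to 47% if 5/5 to 15/5 points are taken out of planning rates that already include grade 1. The first case of the second range shows that the change need not be a loss. The documents do not establish bias from ventilation practice.

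**What to change.** Before analysis, reconcile the Abstract, Endpoints and Power of the study into one binary primary outcome in identical words, stating which grades count, and label the 57% and 29% to match. Two definitions would be coherent:

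- **(a) Thoracic infection:** grade 2 or grade 3, whether or not the patient has been extubated, with grade 1 reported as a secondary outcome.
- **(b) Any respiratory complication, including grade 1:** drop the equation with infections and the confirmation wording that covers every event, and define grade 1 objectively and alike in both arms. This concerns how an event is counted, not when patients should be extubated.

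Report the version not chosen as a sensitivity analysis, and restate the power for the chosen one, saying whether the source rates include grade 1.

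The cost is mainly wording and one power check. The drawback is that the restated power may fall below 80%; under (a) this depends on how many of the events behind the planning rates were grade 1 only.

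### The major/minor complication rule sends every unlisted event to the minor class, so the separate major and minor counts do not measure severity

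*Protocol article*

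**What the plan says.** The Endpoints section lists general morbidity among the secondary endpoints: "Moreover, general morbidity (major and minor) is recorded". It then defines the two classes. For the lower one, "Minor complications are defined as wound infections, venous thrombosis or other". For the upper one, "Major complications consist of- apart from respiratory complications- post-operative bleeding, anastomosis leakage, mediastinitis, and re-operations within the in-hospital period". I read the aside on respiratory complications as adding them to the list; the point below does not depend on that reading.

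The same section states the primary endpoint separately and gives it its own three grades: "The primary endpoint of this study concerns the respiratory complications (i.e. infections) within two weeks after the operation". It also records hospital mortality, readmissions, re-operations and length of ICU and hospital stay as items in their own right.

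The Study objectives section states the trial hypothesis, which begins: "Our hypothesis is that patients undergoing a minimally invasive esophagectomy have fewer morbidity". It does not limit this to major events. The Data collection and statistics section names generic tests and assigns none to the major/minor split.

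**The concern.** The two definitions are not symmetrical. The major class is an enumerated list; the minor class has two named events and a residual. No criterion such as organ failure, return to the ICU or threat to life can raise an event to major. A site that applies the rule faithfully must put a severe but unlisted event under the residual, and so under minor.

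A reader of the results will take major to mean severe. Under this rule a major-complication rate would leave out survivors of infarction, stroke or renal failure who had no listed event. The six centers could also diverge: some would follow the text, while others would override it by judgment and record such events as major. The article does not leave this definition to another document. It states one, and an analysis plan that applied it would inherit the problem.

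**Working it through.** **Step 1. Is the major list closed?** The verbs in both sentences are definitional. In the same paragraph the authors mark operation-related events as examples with *e.g.*, and they do not do so here. The residual appears only in the minor sentence.

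**Step 2. Apply the rule as written.**

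| Event, no re-operation, no listed event | On the major list? | Class under the rule |
|---|---|---|
| Myocardial infarction | No | Minor (residual) |
| Stroke | No | Minor (residual) |
| Renal failure | No | Minor (residual) |
| Venous thrombosis, any consequence | No | Minor (named) |
| Any event leading to in-hospital re-operation | Yes | Major |

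The rule catches severity only where it coincides with a listed name or with re-operation.

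**Step 3. Which trial figures depend on the split?** The sample size does not. Inputs from Power of the study: 57% v 29%, two-sided alpha 0.05, power 0.80. With mean proportion 0.43 and the pooled-variance formula:

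- n = [1.960 × √(2 × 0.43 × 0.57) + 0.842 × √(0.57 × 0.43 + 0.29 × 0.71)]² / 0.28²
- = [1.372 + 0.565]² / 0.0784 = 47.9, so 48 per arm
- 48 / (1 − 0.20) = 60 randomized per arm

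Both stated figures reproduce, and they rest on respiratory infections alone. Total morbidity (major plus minor) does not change when an event moves between classes. Only the two separate counts change.

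**Step 4. How large could the shift be?** The documents give no rate for unlisted severe events, so what follows is illustration under assumptions.

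- *Upper bound.* If 5-15% of patients have such an event: 0.05 × 60 = 3 to 0.15 × 60 = 9 per arm. This assumes that none of them also has a listed major event.
- *Allowing for overlap.* A patient with a respiratory complication is already major. If the two were independent at the planning rates, the misplaced patients would number 3 × 0.43 = 1.3 to 9 × 0.43 = 3.9 in the open arm and 3 × 0.71 = 2.1 to 9 × 0.71 = 6.4 in the minimally invasive arm. Severe events may well cluster in the same patients, so this shows only that the upper bound need not be reached. It does not estimate a direction.
- *Difference between arms.* One patient in 60 is 1.7 percentage points; six in 60 is 10 points. Six requires one arm at the bottom of the assumed range, the other at the top, and no overlap.
- *Loss of power on the major count.* Suppose true major morbidity were 30% v 15%, with 60 per arm and the same share of major-event patients lost from both arms:

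| Share with unlisted events only | Recorded major rates | Power |
|---|---|---|
| 0% | 30% v 15% | 50% |
| 10% | 27% v 13.5% | 45% |
| 25% | 22.5% v 11.25% | 38% |
| 50% | 15% v 7.5% | 25% |

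**The case against.** The strongest reply is that this is loose wording in one secondary split and that severe events are not lost. That is largely right about the reach of the problem. Fatal events appear under hospital mortality, prolonged intensive care under ICU stay (itself named in the hypothesis), and re-operations and readmissions under their own headings. The same rule applies in both arms, so a distorted comparison needs a difference in who is misplaced, and the documents show none. None of this repairs the major and minor counts themselves: a survivor of a stroke without a listed event is still tabulated as minor.

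Three stronger readings are tempting and are not supported.

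- A reader might infer that the morbidity hypothesis is tested on a misclassified endpoint. The hypothesis speaks of morbidity without restriction, the split is described only as recorded, and no test is assigned to it.
- A reader might infer that the rule favors minimally invasive surgery by hiding cardiac or thromboembolic harm from prone positioning, insufflation or longer operating time. The documents link none of these to such events. The Discussion attributes long operating time to open resection.
- A reader might infer that a silent leak seen only on the routine contrast study counts as major. Post-operative management does schedule that study ("At day 5, after gastrographine swallow X ray, the nasogastric tube is retired and started with liquids"), but the article does not say what qualifies as a leak, and such criteria may stand in the full protocol.

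**Conclusion.** The point holds for the separate major and minor complication counts and for nothing wider. The stated rule sorts by event name and defaults every unlisted event to minor, so a severe non-respiratory complication without re-operation is recorded as minor, and venous thrombosis is minor at any severity. The conclusion rests on reading the definitions as they stand and needs no assumed rate. Its numerical effect cannot be derived from the documents: the figures of at most 3 to 9 patients per arm and the power losses rest entirely on assumed rates, and the direction of any between-arm effect is unknown. This is a minor to moderate flaw in a secondary endpoint, worth correcting because correction is cheap.

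**What to change.** Before the data are analysed, remove the residual category as a default to minor. Class every unlisted complication, and venous thrombosis, as major or minor by its consequence, using one pre-specified severity scale applied identically in both arms. Clavien-Dindo with major set at grade III or higher is one suitable choice; another consequence-based scale would also serve. Continue to report bleeding, leakage, mediastinitis, re-operation and the other named events separately, so that nothing now planned is lost.

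The cost is one paragraph in the endpoint definition and one extra field on the paper datasheet. The article does not list the datasheet fields, so it should be checked whether the daily records already hold enough to grade each event. The downside is somewhat less direct comparability with earlier series that used event lists, which separate reporting of the named events largely offsets.
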